## Abstract

**Background:**

Total Knee Replacement (TKR) is the standard treatment for patients with severe knee osteoarthritis (OA). Significant improvement in pain and function are seen after TKR and approximately 80% of patients are very satisfied with the outcome. Functional status prior to TKR is a major predictor of outcome after the intervention. Thus, improving functional status prior to surgery through exercise may improve after surgery outcome. However, results from several previous trials testing the concept have been inconclusive after surgery.

**Methods/design:**

In a randomized controlled trial (RCT) we will test the effect of a pre-operative neuromuscular trainingprogram versus an attention control program on lower extremity function – before and after surgery. We will enroll 80 participants, aged between 55–90 years, who are scheduled for TKR. In this single-blinded RCT, the intervention group will receive a minimum of 8 and a maximum of 24 training sessions plus 3 educational sessions of the knee school. The control group will receive the 3 educational sessions only. Assessments are performed immediately before and after the intervention (before surgery), at 6 weeks, 3 months and 12 months (after surgery).

The primary outcome will include the Chair Stand Test as a measure of leg strength and reaction time. Secondary outcomes are knee function and pain assessed with the self-reported Knee Injury and Osteoarthritis Outcome Score (KOOS). All measurements will be carried out by a specially trained physical therapist, blinded to group allocation.

**Discussion:**

To our knowledge this is the first single-blinded RCT to test the effect of pre-operative neuromuscular training plus knee school against knee school alone – on knee function and pain, assessed immediately after the interventions prior to surgery and repeatedly after surgery.

**Trial registration:**

Clinical Trials NCT00913575

## Background

Osteoarthritis (OA) is the most common joint disorder and a common cause of pain, loss of function and disability in older adults [1]. It is the second most common diagnosis made in older adults seeking medical care [2] and the leading cause of disability at older age [3]. When suffering from severe OA, Total Joint Replacement (TJR) is the preferred treatment option to significantly improve function and pain [2,4]. Given the demographic change with growing segment of the senior population in the Western World, the rate of these procedures will rise exponentially over the next decade. This will result in high health-care expenditures due to the absolute increase in TJR surgery (both direct hospital charges and indirect costs) [5].

The current EULAR (European League Against Rheumatism) recommendations include exercise as an effective treatment in the improvement of pain and function in patients with moderate to severe knee OA (effect size for validated outcome measures of pain and function versus placebo range from 0.57 to 1.0) [6]. Similarly, the OARSI (Osteoarthritis Research Society International) supports the benefits of exercise in patients with knee OA, both on pain and function [7].

Notably, exercise alone may delay but not prevent TJR in severe OA [8]. Similarly, however, TJR does not fully restore function in many patients undergoing the procedure [9-11], which in part may be due to long-term mechanical impairments of the joint.

The most recent review published on pre-operative interventions for patients with hip or knee osteoarthritis awaiting joint replacement was published in 2011 and included 23 trials [12]. The authors concluded that there was low to moderate quality evidence for the benefit of pre-operative exercise for Total Knee Replacement (TKR). These data are consistent with three earlier systematic reviews [13-15].

Considering the evidence from the available formal reviews, two factors may have prevented a benefit from these programs: (A): Four trials had very small groups with a combined total of 137 subjects and were probably underpowered [16-19]. (B): The therapeutic validity as described by Hoogeboom et al. was not sufficient enough, making it unlikely, that interventions evaluated in these studies would have relevant effects [20].

In this study we aim to test a well-defined and feasible training program plus a knee school educational package against the educational package alone on lower extremity function and pain before and after TKR. The trial is powered based on pilot data and includes a detailed assessment of adherence to the program.

### Objective

To study the effect of a pre-operative neuromuscular training plus knee school educational program compared to the educational program alone on lower extremity function and pain in individuals age 55–90 on a waiting list for TKR due to severe knee OA.

### Hypothesis

Primary Endpoint: We hypothesize that patients undergoing a pre-operative neuromuscular training in addition to the educational program will be significantly quicker in performing the Chair Stand Test (test of lower extremity function) compared with those receiving the educational program alone immediately after the intervention and after TKR surgery.

Secondary Endpoints: We hypothesize that patients undergoing a pre-operative neuromuscular training in addition to the educational program will have a greater improvement in function and pain (KOOS subscales) compared with those receiving the educational program alone immediately after the intervention and after TKR surgery.

## Methods/design

### Design

The study design is a single-blinded randomized controlled trial (Figure 1).

**Figure 1 F1:**
[figure not shown]
Flow chart of research design.

Outcomes are measured at baseline (6–12 weeks pre-operative: primary and secondary endpoints), 1 week pre-operative (after the intervention: primary and secondary endpoints), 6 weeks after surgery (secondary endpoints only), 3 months after surgery (primary and secondary endpoints) and 1 year after surgery (secondary endpoints only).

Prior to the baseline assessment eligible patients receive an information package on the study. The package includes detailed information, including their rights when participating in a research project and a written informed consent form. Ethic approval was granted by the Ethics Committee of the Cantons Aargau and Solothurn, Switzerland, approval number 2009/012.

Reporting of the RCT follows the recommendations of CONSORT guidelines for reporting of clinical trials and will be based on intent-to-treat [21]. In addition, a per-protocol analysis will be performed.

### Participants and recruitment

We include individuals age 55–90 years on a waiting list for TKR due to severe primary or secondary OA. Individuals need to also be community dwelling and understand German as a written and spoken language. Exclusion criteria are cognitive impairment, revision surgery for TKR, plans to leave Switzerland before or after surgery, history of inflammatory arthritis and inability to walk at least 3 meters with or without walking aid.

The trial recruits at the Cantonal Hospital Olten and the Cantonal Hospital Aarau, which both perform about 200 TKRs per year. Recruitment and eligibility assessment are conducted by the orthopaedic surgeon at the time of consultation, when the patient has decided to undergo TKR surgery and is placed on the waiting list. Eligible patients are referred to the study centre (Centre on Aging and Mobility, University of Zurich) by fax. The referring surgeon gives eligible patients a one-page summary of the study. After confirming their interest, eligible individuals receive a detailed participant information about the study procedure and 4–7 days later, they are contacted by phone ([name]) to answer additional questions. Eligible and willing individuals then provide their written informed consent. Two experienced physical therapists (assessors), not working at the recruitment sites and not being involved in the neuromuscular training and the knee school, have been specifically trained for the assessments of this study and are blinded to the randomization.

Neuromuscular training and knee school take place at the recruitment sites. Several experienced physical therapists working at the recruitment sites, have been specially trained either for the neuromuscular training or the knee school. Individuals of the intervention group and individuals of the control group were not together in the knee school.

### Baseline assessment and randomization

After informed consent, the assessor performs the baseline assessment at the recruitment site. Additionally, demographics and covariates that affect outcomes are documented: age, gender, height, weight, cognitive impairment (assessed with the Folstein Mini Mental score) [22] and risk of extended inpatient rehabilitation (measured with the Risk Assessment and Predictor Tool (RAPT) [23].

Participants will be randomized using block allocation with a block size of four. The list is computer generated by the independent randomization centre.

The coordinating investigator ([name]) informs the participant about the group allocation and schedules the treatment sessions as allocated by the independent randomization centre.

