#### Intervention group

Participants of the intervention group receive 8–24 sessions of the neuromuscular training program prior to TKR surgery depending on location of the waiting list for surgery. Participants also receive 3 sessions of the knee school starting about 4 weeks before surgery.

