### Analysis plan

All analyses are based on intent-to-treat, including all randomized individuals who had at least 1 intervention session. We will use linear regression to evaluate the effect of our training program plus knee school against knee school alone for both the primary and secondary endpoints – after the training and at 3 months after surgery. The multivariate analyses for the primary endpoint (Chair Stand Test) and secondary endpoints (pain and function subscales of the KOOS) will control for baseline function of the respective endpoint, age in years, gender, and baseline body mass index. To account for the reduced exposure time to the training intervention for participants who were on a short waiting list or were less adherent we will perform subgroup analyses by training exposure groups (we will use the median as a cut-off for lower and higher intensity of the training program based on number of training sessions attended).

To evaluate a benefit of the training program on patient-reported pain and function across all time points, we will use repeated measures linear regression analyses controlling for baseline strength/function, time, age, gender, and body mass index.

Analyses will be conducted with R version 2.14.1 software. All P values are two-sided.

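### Two hospitals recruit and treat, but hospital is absent from the covariates fixed for both regression models: a small loss of precision that is cheap to repair, not a bias

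*Protocol article*

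**What the plan says.** **Sites.** Under Participants and recruitment, the Protocol article states: "The trial recruits at the Cantonal Hospital Olten and the Cantonal Hospital Aarau, which both perform about 200 TKRs per year". The same section adds: "Neuromuscular training and knee school take place at the recruitment sites". On staff it says: "Several experienced physical therapists working at the recruitment sites, have been specially trained either for the neuromuscular training or the knee school".

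**Allocation.** Baseline assessment and randomization gives two facts: "Participants will be randomized using block allocation with a block size of four" and "The list is computer generated by the independent randomization centre". No stratification factor is named, and stratification is not ruled out.

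**Analysis.** Under Analysis plan, the linear regressions for the Chair Stand Test and the KOOS pain and function subscales "will control for baseline function of the respective endpoint, age in years, gender, and baseline body mass index". The repeated-measures regression for patient-reported pain and function has a similar list, with time added. Hospital appears in neither list.

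**The concern.** In a two-hospital trial the hospital is the obvious structural factor. Patient mix, waiting time, knee-school teaching and, for the 3-month endpoint, surgery and rehabilitation may differ between hospitals. If they do, outcomes differ by hospital in both arms. A model without hospital then has two weaknesses.

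- The between-hospital difference stays in the residual, so the treatment effect is estimated less precisely than it could be.
- If one arm happens to hold more patients from one hospital, the estimate obtained is shifted by that imbalance and the model does not correct it.

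The covariate omission matters whichever way allocation was done. With a single unstratified list, blocks of four balance the arms overall but not within each hospital. With lists stratified by hospital, the arms are balanced within hospitals, but a model that ignores the stratification factor reports a standard error that is too large whenever the hospitals differ.

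The article states its adjustment sets explicitly. The point therefore rests on what is written, not on silence that a later analysis plan might fill.

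**Working it through.** **Inputs from the Protocol article.** Sample size calculation: difference in change 7.3 s, within-group SD 7.3 s, alpha 0.05, power 0.90, 25 needed per group, 40 enrolled per group. Analysis plan: two-sided tests. Participants and recruitment: two hospitals with about 200 knee replacements a year each.

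**Assumptions.** Each patient is equally likely to come from either hospital. The hospital difference in outcome, k, is not in the documents. I take k from 0 to 7.3 s (0 to 1 SD), equal in both arms and remaining after the listed covariates. All 80 patients are analysed.

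**1. The plan's own figure.** Normal approximation: n = 2 × (1.96 + 1.2816)² × (7.3/7.3)² = 21.01, so 22 per group. The t-test solution is 22.02, so 23. The stated 25 is within two patients of this, so the planning effect and SD can be used below.

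**2. Chance imbalance under one unstratified list.** The training-minus-control difference in the number of patients from one hospital has SD √(80 × 0.25) = 4.47. As a share of 40 this is 4.47/40 = 0.112, about 11 percentage points. In 95% of simulated trials it stayed within 22.5 points. A count difference of 8 or more (for example 24 against 16) occurred in about 9% of simulated allocations.

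**3. Shift in the realised estimate.** Shift = k × difference in share.
- k = 3.65 s: SD 3.65 × 0.112 = 0.4 s; 95% limit 3.65 × 0.225 = 0.8 s; a 24:16 split gives 3.65 × 8/40 = 0.7 s.
- k = 7.3 s: SD 7.3 × 0.112 = 0.8 s; 95% limit 7.3 × 0.225 = 1.6 s; a 24:16 split gives 7.3 × 8/40 = 1.5 s.

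For comparison, the standard error with no hospital difference is 7.3 × √(2/40) = 1.63 s.

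**4. Precision without and with hospital.** With equal-sized hospitals, k adds (k/2)² to the outcome variance. Without hospital in the model:
- k = 3.65 s: √[(53.29 + 3.33) × 2/40] = 1.68 s; hospital explains 3.33/56.62 = 6% of the variance.
- k = 7.3 s: √[(53.29 + 13.32) × 2/40] = 1.82 s; hospital explains 13.32/66.61 = 20%.

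Simulation agrees (blocks of four, 80 patients, 4,000 runs per scenario; the SD and type I error columns are from the runs with no treatment effect). Pairs are without / with a hospital term:

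| k (s) | SD of estimate (s) | Type I error | Power, effect 7.3 s | Power, effect 4.0 s (assumed) |
|---|---|---|---|---|
| 0 | 1.62 / 1.63 | 4.6% / 4.8% | 99.4% / 99.3% | 68.5% / 67.9% |
| 3.65 | 1.69 / 1.65 | 5.0% / 4.7% | 99.0% / 99.1% | 64% / 66% |
| 7.3 | 1.81 / 1.63 | 4.3% / 5.2% | 97.9% / 99.3% | 57% / 67% |

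The Monte Carlo standard error of a 5% rate in 4,000 runs is √(0.05 × 0.95/4000) = 0.3 percentage points. The mean estimate matched the true effect to within 0.05 s in every scenario, with or without the term.

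**5. If allocation was in fact stratified.** The true SD of the estimate is then about 1.63 s whatever k is. A model without hospital would report about 1.68 s (k = 3.65 s) or 1.82 s (k = 7.3 s) from step 4. Its intervals would be too wide.

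**The case against.** **Bias.** A reader might infer that chance site imbalance distorts the treatment effect. It does not. Over repeated randomisations the estimator is unbiased, and its standard error already covers the extra variation: without the hospital term the simulated type I error was 4.3–5.0%. The shift from a 24:16 split describes one unfavourable draw. This objection stands in full and limits the point to precision.

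**Stratification.** A reader might also infer that allocation was not stratified by hospital. The article mentions one list and no factor, which is suggestive. But it condenses a fuller protocol and does not exclude stratification, so this cannot be asserted.

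**Separate waiting lists and training dose.** The number of sessions varies "depending on location of the waiting list for surgery". That wording hints at hospital-specific lists without stating them. Controls receive no training, so a hospital difference in training dose or trainer quality acts in one arm only. That is a treatment-by-hospital interaction. The calculation above does not model it, and a main-effect covariate would not correct it. These routes therefore do not support the point.

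**Other limits on a hospital effect.** Surgery and rehabilitation cannot affect the pre-operative Chair Stand Test. The two assessors do not work at the recruiting hospitals, so measurement is not done by each hospital's own staff. Baseline value, age, gender and BMI already absorb part of any difference in patient mix. All this makes a difference as large as 1 SD harder to expect, especially before surgery.

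**What survives.** The covariate lists are explicit and omit hospital, and a hospital difference common to both arms remains possible.

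**Conclusion.** The point holds as a minor improvement to the Analysis plan section. Leaving hospital out costs precision if the hospitals differ, leaves a realised site imbalance uncorrected, and ignores a stratification factor if one was used. It does not threaten the validity of the primary comparison.

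The size rests on the assumed hospital difference. The reduction in the SD of the estimate is nil at no difference, about 2% at half an SD (1.69 to 1.65 s) and about 10% at one SD (1.81 to 1.63 s). At the planned effect, power hardly depends on the choice. It would matter noticeably only if the true effect were much smaller than planned and the hospitals differed by about one SD, as in the assumed 4.0 s scenario. Equal hospital sizes and complete data are further assumptions.

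Confidence is high that hospital is missing from both covariate lists. How much that costs cannot be judged from the documents.

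**What to change.** Add hospital (two levels) as a fixed covariate to the linear regressions for the Chair Stand Test and the KOOS pain and function subscales, and to the repeated-measures regression for KOOS. Make the change before outcome data are seen by arm.

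The cost is one degree of freedom. With 80 patients the linear model has six parameters (intercept, arm, baseline value, age, gender, BMI), so residual degrees of freedom fall from 74 to 73. If the hospitals do not differ there is no gain, and simulated power at the planned effect is essentially unchanged (99.4% against 99.3%). No extra patients, visits or data are needed.

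I do not ask for a change to the allocation. Separate lists per hospital with a fixed block of four would make upcoming assignments easier for local staff to predict, and the covariate delivers the precision gain without that drawback.

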#### Knee school

The knee school was designed to educate participants about knee OA, the preparation phase before undergoing TKR and the acute rehabilitation phase afterwards. The concept of the knee school is adapted from the hip school, described by Klassbo [26]. The knee school is taught by an experienced and especially trained physical therapist over 3 individual or group sessions, one session per week, starting about 4 weeks before the operation. Knee school sessions are separately organised for participants of the intervention group and those of the control group to avoid contamination.

The content of the school includes information about anatomy of the knee joint and adjacent functional structures, recommended activities with prosthesis and postoperative pain management, and details on the postoperative rehabilitation phase. Didactical elements include models of the knee joint and the lower extremity, working sheets, photos and videos, hand outs, PowerPoint presentations and peer discussions.

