### Sample size calculation

The sample size calculation is based on the primary endpoint - the Chair Stand Test. We assume that the mean difference in change over time between groups is 7.3 seconds (corresponding to means of 8.3 and 1.0, respectively) and the common within-group standard deviation is 7.3. This effect was selected based on pilot data of an uncontrolled trial in knee OA patients [24], assuming that our control group (without exercise training) would not improve over time while awaiting TKR. It is also assumed that the effect size is reasonable, in the sense that an effect of this magnitude could be anticipated in this field of research. Alpha has been set at 0.05 and the power has been set at 0.9. In each group 25 patients are needed.

Assuming a drop-out rate of 12%, we will include 40 patients per group.

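### A fixed, published block size of four lets anyone who follows the full allocation sequence know up to a third of assignments in advance

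*Protocol article*

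**What the plan says.** Under Baseline assessment and randomization, the protocol article states: "Participants will be randomized using block allocation with a block size of four". It adds: "The list is computer generated by the independent randomization centre". The coordinating investigator then "informs the participant about the group allocation and schedules the treatment sessions as allocated by the independent randomization centre". Consent and the baseline assessment are described before randomisation, but the article does not state the moment at which an allocation is released.

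Under Participants and recruitment there are two hospitals: "The trial recruits at the Cantonal Hospital Olten and the Cantonal Hospital Aarau". On who selects patients: "Recruitment and eligibility assessment are conducted by the orthopaedic surgeon at the time of consultation". On where treatment is given: "Neuromuscular training and knee school take place at the recruitment sites". Only the two outcome assessors, who do not work at these hospitals, are described as blinded.

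Under Knee school: "Knee school sessions are separately organised for participants of the intervention group and those of the control group to avoid contamination". Therapists who teach it can therefore tell the arm.

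The Sample size calculation section gives the target: "we will include 40 patients per group". The article does not say whether the two hospitals share one randomisation list or have one each.

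**The concern.** In a 1:1 block of four, the fourth assignment always follows from the first three, and the third follows from the first two whenever those match. The size is constant and appears in a public document, so a person who has seen the earlier allocations can work out some of the next ones. In an open trial those allocations are not hidden from everyone. The coordinating investigator knows all of them, and the therapists know those at their own hospital.

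At stake is selection before consent. The article describes several steps that leave room for discretion: referral by the surgeon, confirmation of interest, and a telephone call 4–7 days after the detailed information is given. If someone involved knew the next assignment, encouragement or timing could shift with it. The trial has 80 patients, and its primary outcome is a timed test of maximum effort. The Analysis plan adjusts for the baseline value of the endpoint, age, gender and body mass index. None of these would remove a difference between arms in motivation or expected adherence. Central generation of the list protects the list itself, but it does not prevent prediction once the block pattern is known.

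**Working it through.** The article gives no predictability figure, so there is none to reproduce.

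**Inputs.** Block size 4 (Baseline assessment and randomization). 40 patients per group, hence 1:1 and 80 patients in 80/4 = 20 blocks (Sample size calculation). Two hospitals (Participants and recruitment). Equal recruitment by hospital is an assumption, as is the number of patients waiting, because the article gives no accrual rate.

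**1. Observer of the full sequence who knows the block boundaries.** There are 6 equally likely sequences. AABB and BBAA each leave 2 forced assignments; the other 4 leave 1 each.

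- Certain assignments per block: (2×2 + 4×1)/6 = 1.333
- Share: 1.333/4 = 33.3%; over 20 blocks, 20 × 1.333 = 26.7 of 80
- Chance of a correct best guess at positions 1 to 4: 1/2, 2/3, (1/3)(1) + (2/3)(1/2) = 2/3, and 1
- Mean: (0.500 + 0.667 + 0.667 + 1.000)/4 = 70.8%

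**2. Staff who see only their own hospital.** If each hospital has its own list, case 1 applies: 33.3% and 70.8%. If both share one list, and each earlier patient in the block was at the own hospital with probability 1/2:

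- Position 3 is certain if both earlier patients were at the own hospital (1/4) and their arms match (1/3): 1/12
- Position 4 is certain if the two earlier patients who share an arm were both at the own hospital: 1/4
- Share: (0 + 0 + 1/12 + 1/4)/4 = 1/12 = 8.3%

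A simulation of 80 patients gave 8.4% certain and a best guess right 60.0% of the time. This still grants the observer knowledge of the block boundaries.

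**3. Patients waiting between referral and randomisation.** Take an observer who knows all past allocations, but with one patient ahead who is not yet randomised. Positions 1 and 2 then give no information. At position 3 one allocation is known, so the guess is right with probability 2/3. At position 4 two are known, and they match with probability 1/3.

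- Certain: (1/4)(1/3) = 8.3%
- Best guess: (1/2 + 1/2 + 2/3 + 2/3)/4 = 58.3%
- With two ahead: 0% certain, and (1/2 + 1/2 + 1/2 + 2/3)/4 = 54.2%

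**4. Randomly varied block sizes.** Simulated for 80 patients, with the sizes equally likely and an observer who knows the set of sizes and sees every past allocation:

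| Block sizes | Certain | Best guess right |
|---|---|---|
| 4, fixed | 33.3% | 70.8% |
| 4 and 6 | 5.6% | 69.1% |
| 4, 6 and 8 | 2.4% | 67.8% |

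With 4, 6 and 8, about 80 × 0.024 = 1.9 assignments are certain, against 26.7 now. The gain is mainly the removal of certainty; a good guess remains possible for someone who sees everything.

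**The case against.** The strongest reply is that the people who select patients are not shown to know the allocations. The surgeon judges eligibility at the consultation and refers by fax to a study centre elsewhere. The staff who do see allocations are therapists, and none is described as recruiting. Treatment at the recruiting hospital shows a shared location, not shared knowledge. This stands. A reader might infer that surgeons can foresee a third of assignments and steer referral accordingly, but the article does not support that.

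Timing is a second reply, and it also stands. Between referral and randomisation come information, the telephone call, consent and baseline assessment. A surgeon who refers today does not know which list position the patient will take, and one patient in the queue already lowers certainty to 8.3%.

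A reader might also infer that the coordinating investigator makes the telephone call before consent and so could act on a predicted assignment. Names are removed from the text, so this cannot be told.

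Independent list generation, and consent and baseline described before randomisation, reduce the scope for selection after consent. Blinded assessors from outside the hospitals protect the measurement of the outcome. None of these prevents prediction before consent by a person who follows the sequence, and the coordinating investigator is placed to follow it whether there is one list or two.

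Finally, varying the block sizes barely lowers the full observer's best guess (70.8% to about 68%). That is correct and limits what the change can be said to achieve.

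**Conclusion.** The point holds as a vulnerability in the randomisation procedure. A single block size of four is fixed and published in an open-treatment trial, and at least one role learns every allocation. For that role, up to 33.3% of assignments (about 27 of 80) are certain in advance and the best guess is right 70.8% of the time, provided the block boundaries are known. For staff who see one hospital only, the certain share is about 8% with a shared list and equal recruitment, and up to 33% with a list per hospital. It is lower in either case when patients are queued. The article does not settle which list structure applies.

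It would go too far to say that a third of assignments are predictable to those who recruit, or that any steering has taken place; nothing in the article shows either. This is an improvement worth making because it is cheap, and it does not invalidate the design.

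Whether hospital should be a covariate in the regression models is a separate, optional question. It has no bearing on concealment.

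**What to change.** Have the independent randomisation centre generate the remaining list with randomly varying block sizes, for example 4, 6 and 8. Withhold the sizes from the coordinating investigator, the surgeons and the therapists. Release each allocation only after consent and baseline assessment are recorded, and say so in the protocol. State also whether the hospitals share one list.

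Do not add stratification by hospital as part of this change. If the list is currently shared, separate lists would give each hospital's staff a complete sequence to follow, and their best guess could rise from about 60% to about 68% even with varied blocks.

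The cost is one regenerated list at the randomisation centre and possibly a small imbalance in final arm sizes. Certain assignments fall from 33.3% to about 2%, even if the set of sizes becomes known.
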